### Aim 3: Describe factors associated with practice adoption, implementation, and maintenance of PATHWEIGH.

#### Outcomes and Measures

##### Practice member surveys

A baseline (pre-intervention) survey will be given to all practice members to assess personal characteristics (PRISM element of recipients) and practice culture, implementation climate, and perception of system priority for weight management (PRISM elements of implementation and sustainability infrastructure, and intervention). Clinicians will also be assessed on current weight management practices and their self-efficacy and satisfaction with obesity treatment (PRISM elements of recipients and intervention). These surveys will be repeated at 1 year after PATHWEIGH implementation for comparison pre-post intervention.

##### Provider, staff, and patient interviews

A purposeful selection of providers and staff, estimated at three to six total per practice, will be interviewed to assess RE-AIM outcomes. Practice staff and clinician interviews will focus on factors influencing adoption of PATHWEIGH and use of the PATHWEIGH implementation strategies, as well as influences on appropriate use of PATHWEIGH. Interviews will seek to understand the context of the delivery as well as the mindsets and belief systems driving thoughts and actions about what happens. External influences such as financial demands and staff turnover will be explored as potential sources of implementation difficulty (PRISM elements of recipients, intervention, implementation and sustainability infrastructure, external environment). Patient interviews (estimated at 40 total per year for each of the three cohorts) will explore their perspectives and experience with the intervention.

##### Other data collection

Observations will be conducted by research assistants at 3-6 months post-implementation. Research assistants will shadow selected patient visits to determine fidelity and quality of patient-provider communication on weight. A fidelity checklist and extensive field notes will be used. General practice observations will also be conducted to illuminate how the implementation works in practice and where there may be leakage, slippage, or gaps occurring in care processes in the intervention. Use of PATHWEIGH will also be extracted from Epic during the scheduled data query periods to determine clinicians’ use of PATHWEIGH tools as a measure of adoption. Additionally, research assistants will conduct key informant interviews with selected staff in practices to assess the cost and resources needed to implement PATHWEIGH and the associated implementation strategies. To assess financial sustainability, clinical billing data will be extracted from Health Data Compass to assess reimbursement for the weight-prioritized visits using standardized Medicare reimbursement rates.

#### Analysis

Quantitative analysis of the reach, adoption, implementation, and maintenance outcomes in Table 3 will be conducted using survey responses and fidelity checklists. Data will be analyzed descriptively (e.g., means, proportions) and estimated pre- and post-intervention. Inferential comparisons regarding association of the intervention with outcomes will be based on paired t-tests (continuous variables), McNemar’s chi-square tests (categorical variables), or generalized mixed modeling to adjust for potential confounders.

Qualitative methods, including interviews and observations, will be used to determine contributions to the adoption, implementation, and maintenance outcomes and PRISM contextual factors affecting these outcomes. Interviews will be audio-recorded, transcribed, cleaned, and entered into the qualitative software program, ATLAS.ti. We will use a grounded theory hermeneutic editing approach [48] to identify issues regarding intervention implementation from the perspectives of providers, staff members, leaders, and patients. Codes will be identified and created based on emergent elements in the data and will be used to tag relevant text from the transcripts. Quotation reports, which list all the associated quotations verbatim, will be generated and then organized by practice. The qualitative core group will hold ongoing meetings to read through all the quotations for these codes and categorize text that exemplifies the identified constructs. After initial thematic groupings, member-checking will be completed with key practice members. Additionally, we will use a matrix approach to determine patterns of emergent concepts across PRISM contextual factors and across practices.

Using a mixed methods concurrent parallel design, each element of data collection will occur separately [49]. Specifically, quantitative data will be collected and analyzed, and the qualitative data will be collected and analyzed. Then the two sets of data will be analyzed and interpreted together. Specific methods will include both a matrix approach and a data transformation approach to mixing of the data. Joint display tables describing the interplay of the quantitative and qualitative results will be created [50]. To achieve our aims, we will use the analysis technique of qualitative comparative analysis (QCA) [51]. QCA applies set theory to identify *necessary* and one or more *sufficient* sets of conditions to produce favorable outcomes, in this case, to determine what sorts of practice conditions and structures were needed to effectively implement PATHWEIGH [51, 52]. The fuzzy-set variant (fsQCA) allows simultaneous use of qualitative and quantitative data. It is newly applied to practice transformation [53], and we are using it in other work [54]. We will use this analysis to merge information from all sources and evaluate the contribution of specific PRISM factors on the outcome of intervention implementation and our practice break-even measure from the cost analysis. We will use the process detailed by Rihoux and Ragin and the fsQCA software [51].

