### Study setting

This study will be conducted in 57 family medicine and general internal medicine clinics within a large, multi-specialty health care system in Colorado (Fig. 1). One primary care clinic was excluded as it was a pilot test site [29]. These practices are comprised of approximately 400 clinician full-time equivalents (physician, nurse practitioner, physician assistant) caring for nearly 500,000 patients in diverse geographic and socioeconomic contexts. All practices have the following resources for the implementation of obesity management: access and full use of the Epic EMR, practice quality improvement facilitators, standardized workflows for medical assistants, funds for site innovation, inter-connectedness to the system at large, and regular training opportunities. Primary care leadership has unanimously offered their support for this project.

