**Clinician and clinic staff-specific outcomes**			
Clinic characteristics	# and characteristics of clinicians and patients empaneled to the clinic	Survey to practice leadership	Baseline
Practice culture	Practice culture scale [40, 41]	Survey to providers and staff	Baseline and 1-year post-intervention
Implementation climate	Implementation climate scale [42, 43]	Survey to providers and staff	Baseline and 1-year post-intervention
History of practice improvement	# and type of practice improvement in the past year	Survey to providers and staff	Baseline and 1-year post-intervention
Self-efficacy and satisfaction	One item assessment of perceived confidence in ability to provide weight management, one item assessment of perceived satisfaction	Survey to providers and staff	Baseline and 1-year post-intervention

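### Aim 3 lets clinic-delivered pre/post survey changes be tested as independent pairs with no calendar-time term, so p-values can be too small and secular change can be read as an effect of PATHWEIGH

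*Protocol article*

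**What the plan says.** The Analysis section of Aim 3 in the protocol article sets out descriptive summaries first and then the tests: "Inferential comparisons regarding association of the intervention with outcomes will be based on paired t-tests (continuous variables"), McNemar tests for categorical variables, "or generalized mixed modeling to adjust for potential confounders". It gives no rule for choosing among the three and mentions neither clinic clustering nor calendar time.

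The outcomes it covers are defined in the same section: "Quantitative analysis of the reach, adoption, implementation, and maintenance outcomes in Table 3 will be conducted using survey responses and fidelity checklists". Practice culture, implementation climate, self-efficacy and satisfaction stand in a separate block of Table 3, with timing "Baseline and 1-year post-intervention". They enter a pre/post comparison through the section on practice member surveys: "A baseline (pre-intervention) survey will be given to all practice members", and "These surveys will be repeated at 1 year after PATHWEIGH implementation for comparison pre-post intervention".

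The other aims are handled differently. The Aim 1 primary model has random intercepts for patient, provider and clinic, and treats calendar time as categorical in four one-year periods. The Aim 2 mediation analysis accounts for clustering within clinics and providers and adjusts the outcomes model for time.

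**The concern.** PATHWEIGH is switched on clinic by clinic, and training, consultation support and practice facilitation arrive with it (Design and randomization; Implementation strategies). Colleagues in one clinic share that exposure, so their changes on a culture, climate or confidence scale may move together. Paired t and McNemar tests on individuals assume that the pairs are independent.

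These tests also have no term for time. The two surveys are at least a year apart, and the Background describes primary care as changing quickly. Any change that would have happened anyway is counted as change associated with the intervention.

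The article calls these comparisons inferential and ties them to the intervention. As worded, an unclustered person-level p-value would comply fully with the plan. What is at stake is a spurious statement that PATHWEIGH changed practice outcomes, which would then be merged with the qualitative data when implementation is interpreted.

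**Working it through.** The article states no sample size, ICC or alpha for Aim 3, so there is no Aim 3 figure to reproduce. The check shows how the named tests behave over a range of assumptions.

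**Inputs**
- Clinics: "This study will be conducted in 57 family medicine and general internal medicine clinics" (Study setting).
- Respondents per clinic, m: not stated. As a proxy, "These practices are comprised of approximately 400 clinician full-time equivalents" gives 400 / 57 = about 7. This is an assumption. Full-time equivalents are not a head count, other staff are surveyed too, and non-response and turnover work the other way. Range used: 5 to 20.
- Clinic ICC of the change score, ρ: not stated, so assumed at 0 to 0.10. The 0.02 to 0.05 under Sample size concerns the patient weight outcome. The relevant ρ is that of the change, because a stable clinic difference cancels in each pair.
- Nominal alpha 0.05, two-sided, borrowed from the Aim 1 power statement.

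**Step 1: clustering.** Design effect DE = 1 + (m − 1)ρ. Real type I error = 2 × [1 − Φ(1.96 / √DE)].

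| ρ | DE at m = 7 | 1.96 / √DE | Type I error | Simulated |
|---|---|---|---|---|
| 0 | 1.00 | 1.96 | 5.0% | 5.3% |
| 0.02 | 1.12 | 1.85 | 6.4% | 6.3% |
| 0.05 | 1.30 | 1.72 | 8.6% | 7.8% |
| 0.10 | 1.60 | 1.55 | 12.1% | 12.5% |

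The simulation used 57 clinics, 7 pairs each and 4,000 runs. In the same runs a t-test on the 57 clinic-mean changes rejected 4.5% to 5.2% of the time. Over m = 5 to 20 and ρ = 0.01 to 0.10, the formula gives 5.5% (m = 5, ρ = 0.01) to 25.0% (m = 20, ρ = 0.10).

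**Step 2: secular change.** Take 57 × 7 = 399 pairs, ρ = 0 and no intervention effect. A drift of d SD of the change score is declared significant with probability close to Φ(d√399 − 1.96). For d = 0.1: 0.1 × 19.97 = 2.00, which gives about 52%. For d = 0.2 it is about 98%, and for d = 0.05, with the opposite tail included, about 17%. The size of any drift is an assumption. That it would be credited to the intervention is not.

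**Step 3: can time be separated?** Table 3 gives two waves per clinic and no calendar date for baseline. With categorical periods as in Aim 1, the design matrix shows:
- One common baseline date: rank 4 with and without the intervention column. Every post-baseline period contains only intervention surveys, so the two effects cannot be separated.
- Baseline just before each crossover: rank 5 with the column and 4 without. They separate, but only by comparing clinics with each other, as a random-effects model does.
- Within-clinic pairs alone (clinic fixed effects): rank 60 both ways, under either timing. Paired changes never separate them.

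**Step 4: which mixed model.** Random intercepts for respondent and clinic alone are not enough. Both cancel in the pre/post contrast, so correlated change within a clinic stays unmodelled. A clinic-by-wave (random pre/post) effect is needed.

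**The case against.** The strongest reply is that the article does not commit the trial to unclustered tests. The same sentence names mixed modeling, which could carry clinic and period terms, and an article may leave model terms to fuller documents. Nor does it say that the pairs are individuals. Culture and climate are practice-level constructs, and a paired t-test on clinic means is still a paired t-test with correct error. Aim 3 is framed as descriptive.

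Much of this stands, and it rules out several stronger readings:
- A reader might infer that the p-values are too small. The documents support only that they can be: this needs person-level pairs and correlated change, and the article fixes neither.
- A reader might infer that the plan must ignore clustering and time. It leaves the choice open.
- A reader might infer that Hypothesis III rests on these tests. It also draws on interviews, observations and qualitative comparative analysis, and several RE-AIM measures, such as use of PATHWEIGH tools, have no pre-period to compare.
- A reader might infer that the staggered sequences can always separate time from intervention. Step 3 shows that this depends on an unstated baseline date.

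What does not stand is that the mixed-model option settles the matter. It is joined by an unranked alternative and is given one purpose, confounding. The article names the tests itself, so this is a stated method that can give wrong error rates and not simply an omitted detail.

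**Conclusion.** The concern holds in conditional form. If individual pairs are tested, the real type I error of a nominal 5% test is about 5% to 12% for 7 respondents per clinic and a change-score ICC of 0 to 0.10. Both inputs are assumptions. Larger clinics or stronger correlation push it higher, and at an ICC of 0 there is no inflation. The confounding with calendar time needs no ICC assumption and affects any simple pre/post test, including one on clinic means. The consequence is confined to Aim 3: the primary and secondary weight analyses use their own models and are untouched. It is worth correcting before the surveys are analysed, but it does not threaten the trial's main result.

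**What to change.** Replace the sentence on inferential comparisons so that inference rests on a cluster-respecting analysis, one of:
- a (generalized) mixed model with random effects for respondent and clinic plus a clinic-by-wave (random pre/post) effect; or
- a paired test on clinic-mean changes.

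State when the baseline survey takes place in each sequence. If it is staggered with crossover, add a calendar-period term. Only the mixed model can use it, because clinic-mean pairs cannot separate period from intervention. If baseline is one common date, report the results as descriptive pre-post change and not as association with the intervention. Keep person-level paired t and McNemar results as description only.

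The cost is a few lines of wording and somewhat wider intervals. Mixed modeling is already listed and the surveys are already planned. Where the period term is added, precision will depend on between-clinic comparison.

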### Return on investment

A formal return on investment (ROI) analysis will estimate the cost associated with adopting, implementing, and maintaining the intervention in practices and compare this to the difference in reimbursements before and after implementation in each practice. We will adapt a time-driven activity-based costing questionnaire that we have used in several previous studies [55, 56] for the estimation of the cost of staff time used in delivering the SOC and PATHWEIGH visits (including time of PATHWEIGH consulting obesity certified providers), practice facilitation support, and time clinic staff participate in training. In addition, we will measure the cost of materials provided to patients, hiring costs (if any), and other administrative costs incurred for all aspects of PATHWEIGH. To generalize to other settings, we will use industry average compensation costs for providers and staff to value time-driven costs as well as health system average compensation costs for the ROI analysis. Reimbursement data from the health system billing system will be collected for both the control and intervention period. We will collect clinic-level revenue as well as the Medicare allowed amounts for weight-prioritized visits. In addition, for the system-level ROI, we will obtain total system revenue for those patients that have a weight-prioritized visit in each calendar year. A practice perspective ROI will be calculated comparing the PATHWEIGH implementation cost to the difference in reimbursement for weight-prioritized visits during PATHWEIGH implementation and control periods. A system perspective ROI will compare the PATHWEIGH implementation cost to the difference in annualized revenue for patients with a weight-prioritized visit under the PATHWEIGH and control condition.

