### Participant eligibility criteria

Patients eligible for this analysis must (1) be aged 18 years or older, (2) be overweight (BMI ≥25 kg/m^2^) at initial visit, and (3) have had at least one weight-prioritized visit in a participating clinic. Exclusion criteria in the original protocol include limited cognitive ability, have a non-home residence, or have less than 1-year life expectancy. Ultimately, these were not applied due to the inability to obtain the necessary fields in the data extraction; however, the number of individuals that would be excluded based on these criteria is expected to be minimal and balanced across the study arms. Weight-prioritized visits are defined as the chief complaint or reason for the visit being at least one of the following: (1) “overweight,” “obesity,” or “weight,” (2) ICD-10-CM codes for billing E66–E.66.9, Z68.25–45, (3) use of the “obesity brief HPI” Epic flowsheet, or (4) the PATHWEIGH patient questionnaire.

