**Fig. 4 Fig4:**
[figure not shown]
PATHWEIGH clinic flow

**Table 2 Tab2:** Key components of PATHWEIGH and PATHWEIGH implementation strategies

***PATHWEIGH is a weight management care path built into Epic.*** It includes: • Weight-prioritized visit type: Defines the scope of the visit for the patient and provider. • Time-efficient documentation and data capture: Patient questionnaire completed prior to the visit captures history around weight gain and barriers to weight loss that can guide the patient-clinician conversation and treatment plan. • Clinical decision support: SmartSet in Epic suggests weight loss approach(es) based on patient BMI and preferences according to the Obesity Society guidelines [32]. • Tracking: Displays progress with weight loss and weight loss maintenance during patient visits to guide the patient-clinician conversation and evolving treatment plan over time. • Diagnosis and billing: Tool in Epic automatically adds the diagnosis of overweight (for BMI 25-29.9 kg/m^2^) or obesity (for BMI> 30 kg/m^2^) and links the most common weight-related co-morbidities (according to the Center for Medicare and Medicaid Services) to ensure adequate provider reimbursement.	
***PATHWEIGH implementation strategies*** include: • Practice facilitation: Practice facilitators drive implementation efforts by working with practice-selected Practice Champions, engaging leadership in goal setting and monitoring along system and practice goals, and utilizing quality improvement techniques for supporting adoption, implementation, and management of PATHWEIGH. • Clinician education: Online e-learning module on evidence-based weight management treatment which includes 2 credits of continuing medical education. • Consultation support: built-in to Epic consultation support for clinicians by request; built-in to Epic availability of UpToDate, a subscription-based clinical reference.	

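### The practice ROI counts revenue only from visits labelled weight-prioritized, a label PATHWEIGH can itself confer, so it tends to overstate the return; the system ROI uses the same label, with uncertain direction

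*Protocol article*

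**What the plan says.** The Return on investment section opens broadly: the plan will cost the intervention and "compare this to the difference in reimbursements before and after implementation in each practice". The two working definitions that follow are narrower. The practice-perspective ROI is obtained by "comparing the PATHWEIGH implementation cost to the difference in reimbursement for weight-prioritized visits during PATHWEIGH implementation and control periods". The system-perspective ROI sets the same cost against "the difference in annualized revenue for patients with a weight-prioritized visit under the PATHWEIGH and control condition", for which "we will obtain total system revenue for those patients that have a weight-prioritized visit in each calendar year". On the data for the practice side the section says: "We will collect clinic-level revenue as well as the Medicare allowed amounts for weight-prioritized visits".

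The label is defined under Participant eligibility criteria. One sufficient route is "ICD-10-CM codes for billing E66–E.66.9, Z68.25–45"; another is "the PATHWEIGH patient questionnaire". Table 2 lists as a PATHWEIGH component: "Tool in Epic automatically adds the diagnosis of overweight" or obesity. Under Current standard of care, control clinics have no access to the PATHWEIGH tools. Clinician workflow allows the tools to be used when weight comes up spontaneously, and Staff workflow leaves each clinic or provider to decide how many weight-prioritized visits to offer.

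The Aim 1 analysis recognises that PATHWEIGH may raise the number of such visits. It adds an analysis of everyone eligible by age and BMI, but for the weight outcomes only.

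**The concern.** A return on investment should count revenue that exists because of the program. The label-based difference also counts two things that do not qualify. One is a visit that would have taken place and been billed anyway, but now carries a diagnosis code or a completed questionnaire that brings it under the label. The other is a weight visit that fills a slot another billable visit would have used. In both cases the whole reimbursement enters the intervention-period total, while the clinic's income changes only by any genuine uplift per visit.

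The practice break-even measure from the cost analysis also feeds the qualitative comparative analysis under Aim 3, and the Dissemination section foresees wider deployment through Epic. An overstated practice return would carry into both.

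**Working it through.** The plan states no ROI figure, so there is nothing to reproduce. The check sets the definitions side by side and then uses an accounting identity with assumed inputs.

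**1. Can the program change the label?** Yes, by three routes in the text: the automatic diagnosis (Table 2) feeds the billing-code criterion; the questionnaire criterion cannot be met in a control period without the tools; and spontaneous use can bring an existing visit under the label.

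**2. Practice ROI.** Let k be the extra labelled visits, R the reimbursement per labelled visit, s the share of the k visits that relabel or displace a visit billed anyway, and u the true proportional uplift over that visit.
- Credited by the stated formula: k·R.
- Truly incremental: k·R·[(1−s) + s·u/(1+u)].
- Ratio with u = 0: 1/(1−s).

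None of these inputs is in the document. Over assumed ranges:

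| s | ratio, u = 0 | ratio, u = 0.2 |
|---|---|---|
| 0 | 1.00 | 1.00 |
| 0.25 | 1.33 | 1.26 |
| 0.50 | 2.00 | 1.71 |
| 0.75 | 4.00 | 2.67 |
| 0.90 | 10.0 | 4.00 |

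For example, at s = 0.5 and u = 0.2: 0.5 + 0.5 × 0.2/1.2 = 0.583, and 1/0.583 = 1.71.

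**3. Scale.** Table 1 gives a sequence 1 median of 10,589 visits per clinic in 2019. If 1% to 5% (assumed) were merely relabelled, 0.01 × 10,589 = 106 to 0.05 × 10,589 = 529 visits' reimbursement per clinic-year would be credited with no change in income.

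**4. Effect on an ROI (all inputs assumed).** Take 500 extra labelled visits at $100 and u = 0, so ROI = [50,000·(1−s) − cost]/cost.
- Cost $40,000: +25% as planned; −6% at s = 0.25; −37.5% at s = 0.50.
- Cost $20,000: +150% as planned; still +25% at s = 0.50.

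**5. System ROI (assumed).** Let labelled patients go from 100, each with revenue 1.5, to those 100 plus 100 more, each with revenue 1.0. Nobody's revenue changes.
- Summed: (150 + 100) − 150 = +100.
- Per patient: 250/200 − 150/100 = −0.25.
- Over all eligible patients: 0.

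Selection by label distorts both versions, but not in the same direction.

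**The case against.** Several counter-arguments have weight.

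- **Part of the difference is real.** Linking comorbidities is meant to secure reimbursement, and some extra visits will be truly additional. Whether weight visits pay for themselves is a legitimate question, and Other data collection frames financial sustainability that way. This stands: the label-based figure is worth keeping, as a gross figure.
- **Costs move with the label too.** The plan costs staff time for delivering both kinds of visit. If that cost is attributed by label, each relabelled visit adds an error of revenue minus delivery cost, not full revenue. This stands as a partial offset; the plan does not say how the attribution is done.
- **The formula might mean revenue per visit.** For the practice ROI this is hard to sustain, because the difference is set against an implementation cost and must therefore be a total. For the system ROI the article does not settle it.
- **Total clinic revenue is noisy.** At the assumed $100, 500 visits are $50,000 against 10,589 × $100 = $1,058,900, about 5%. This stands, and argues for reporting both figures rather than replacing one with the other.

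A reader might also infer three stronger claims that the document does not support. The first is that PATHWEIGH labels every visit by an eligible patient; Clinician workflow makes use of the tools optional, and the Aim 1 analysis speaks only of a potential increase. The second is that the system ROI is necessarily biased upward; that follows only if revenue is summed. The third is that the financial conclusion will change sign; in step 4 that depends on the assumed cost.

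**Conclusion.** The point holds for the practice ROI. Its revenue term is tied to a label that the program can confer, with no all-visit counterpart, although the section's own opening sentence speaks of practice reimbursement generally. Credited revenue exceeds incremental revenue whenever some labelled visits were relabelled or displaced others. The factor is 1/(1−s) without per-visit uplift and smaller with it; there is no excess if every extra visit is additional. The true s is unknown, and attributing delivery cost by label would offset part of the error.

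For the system ROI the conclusion is weaker: selection by the same label distorts it, upward if revenue is summed and in either direction through case mix if averaged per patient.

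This concerns the economic evaluation only; the weight outcomes are unaffected. It is an inexpensive improvement, not a flaw in the trial's main inference.

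**What to change.** **Practice ROI.** Bring the formula into line with the section's opening sentence. Beside the label-based figure, described as gross, report a practice ROI based on the change in total clinic reimbursement over all visits. Adjust it for calendar period using the stepped-wedge structure. Do not adjust for visit volume, since that would also remove truly additional visits. Do not present the label-based figure alone as net return, or use it alone as the break-even input to the qualitative comparative analysis. State whether delivery cost is attributed by label.

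**System ROI.** State whether revenue is summed or averaged per patient. If the revenue extract can be widened, add a version over all patients eligible by age and BMI, as the Aim 1 analysis already does for weight.

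**Cost.** The practice change is mainly wording if the clinic-level revenue to be collected covers all visits. The sentence can also be read as limited to weight-prioritized visits, so this should be confirmed. The all-visit estimate will be noisier because weight visits are likely to be a small share of clinic revenue. The wider system version is not covered by the planned extract and needs additional data.

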### Data collection and management

De-identified data will be extracted from Epic (the electronic medical record) from March 17, 2020, to March 16, 2021, then every 6 months from March 17, 2021, until September 17, 2025. The study timeline is depicted in a SPIRIT diagram in Fig. 3. Data extraction will be performed by Health Data Compass, the Colorado Center for Personalized Medicine’s cloud-based enterprise data warehouse and management platform. Health Data Compass extracts de-identified data using a proprietary process, wherein all data are checked for process compliance and missingness prior to release to the study team. As these data are de-identified, informed consent was not utilized. However, a written informed consent process was utilized for specified, individually contacted patients and practice members for the purposes of the implementation evaluation.

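### The system-level ROI takes gross system revenue as the return but sets only PATHWEIGH implementation cost against it, so its sign can be wrong

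*Protocol article*

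**What the plan says.** All of the following is in the Return on investment section of the protocol article, except where stated.

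- **Return, system perspective.** For this analysis "we will obtain total system revenue for those patients that have a weight-prioritized visit in each calendar year". The revenue is not restricted to any type of service.
- **Comparison, system perspective.** "A system perspective ROI will compare the PATHWEIGH implementation cost to the difference in annualized revenue" for these patients between the PATHWEIGH and control conditions.
- **Costs.** The analysis "will estimate the cost associated with adopting, implementing, and maintaining the intervention in practices". The components are "the cost of staff time used in delivering the SOC and PATHWEIGH visits" (with the time of consulting obesity-certified providers), "practice facilitation support, and time clinic staff participate in training", patient materials, any hiring, and "other administrative costs incurred for all aspects of PATHWEIGH".
- **Comparison, practice perspective.** Implementation cost is set against "the difference in reimbursement for weight-prioritized visits during PATHWEIGH implementation and control periods".

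Aim 2 (Outcomes and measures) names anti-obesity medication and endoscopic or surgical bariatric procedures as patient-level mediators. The Clinician workflow section says that the SmartSet flags consideration of bariatric surgery and offers orders for tests, referrals and procedures.

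**The concern.** An ROI is read as net gain per unit spent. The system version puts revenue from every service on one side. On the other side it puts only the cost of the weight-prioritized visits and of the PATHWEIGH programme. A procedure or a specialist referral brings in revenue, but it also uses theatre time, staff and supplies. Those costs appear nowhere in the list, and no margin is applied to the revenue, so gross revenue stands in for net return.

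The gap lies on the route by which the intervention is expected to work. If PATHWEIGH leads to more bariatric procedures, the revenue side grows by the full payment while the cost side does not move. Where payment is per service, any billed event raises the figure whatever it cost to deliver, and care avoided through better health lowers it. At stake is whether a reader of the system ROI can tell if the health system gained or lost money.

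**Working it through.** **Figures in the article.** There is no ROI, revenue, cost or margin figure to reproduce, so the check is algebraic.

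**Scope of the two sides**

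| | Revenue counted | Cost counted |
|---|---|---|
| Practice ROI | Weight-prioritized visits | Staff time for those visits, plus programme costs |
| System ROI | All system services for these patients | The same list |

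The practice version is roughly matched. The system version widens the revenue and leaves the cost where it was.

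**Definitions**

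- C: PATHWEIGH implementation cost, C > 0.
- dR: difference in system revenue between conditions.
- m: share of dR left after the cost of delivering the services behind it, excluding anything already in C. The article does not give m, so every value below is an assumption.

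**Formulas.** The article says only that the two amounts will be compared. I assume the conventional form:

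- As defined in the article: ROI = (dR − C)/C. It is positive when dR > C.
- Net of service cost: ROI = (m·dR − C)/C. For m > 0 it is positive when dR > C/m.

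For 0 < m < 1 the first is positive and the second negative exactly when C < dR < C/m. A simple difference (dR − C) or a ratio judged against 1 gives the same window, so the sign result does not depend on the form assumed.

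**Window of dR/C in which the sign is wrong (from 1 to 1/m)**

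| Assumed m | 1/m | Window |
|---|---|---|
| 0.05 | 20 | 1 to 20 |
| 0.10 | 10 | 1 to 10 |
| 0.20 | 5 | 1 to 5 |
| 0.30 | 3.33 | 1 to 3.33 |
| 0.50 | 2 | 1 to 2 |
| 0.80 | 1.25 | 1 to 1.25 |
| 1.00 | 1 | none |

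If the extra services break even or lose money (m ≤ 0), the sign is wrong for every dR > C.

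**Illustration with dR = 3C (hypothetical).** As defined in the article: (3C − C)/C = +200%. Net of service cost:

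- m = 0.10: 0.3 − 1 = −70%
- m = 0.20: 0.6 − 1 = −40%
- m = 0.30: 0.9 − 1 = −10%
- m = 0.50: 1.5 − 1 = +50%

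**Effect of one more billed service.** Each extra dollar of revenue raises the ROI as defined by 1/C. Net of service cost the change is m/C, which is a fall if m < 0. In that case the error can also run the other way. At m = −0.30 the net ROI is positive once dR/C < −3.33, while the ROI as defined is strongly negative.

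**The case against.** **Condensed article.** It can be said that the netting of revenue may be set out in a fuller plan, since the costing builds on earlier questionnaires. This does not remove the point. The article itself states what counts as return, what counts as cost, and that one is compared with the other.

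**Unknown size.** No margin is given, and at a high margin the problem is small: at m = 0.80 the window is only 1 to 1.25. This stands. A reader might infer from a low assumed margin that the return is overstated by some large multiple. The documents support no such multiple.

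**Payment model.** A reader might infer that every complication raises the ROI. That holds only where payment is per service. Under capitated or bundled payment the revenue may not rise, and the Background section itself notes the growth of value-based models. The cost of the service would still go uncounted.

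**Importance.** A reader might take the system ROI to be the business case for spreading PATHWEIGH. The article does not say so. The Dissemination section does not mention ROI, and the Aim 3 analysis carries forward a practice-level break-even measure.

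**Calendar years.** A reader might also infer that revenue pulled by calendar year mixes SOC and PATHWEIGH time in each switch year. The documents do not support this. The comparison is of annualized revenue by condition, which can accommodate part-years. The calendar-year phrase may define the patient group and not a revenue window, and the Aim 1 analysis uses calendar time for the study periods. The March dates ("then every 6 months from March 17, 2021, until September 17, 2025") are extraction dates, not stated switch dates.

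**Conclusion.** The mismatch is real, and it is stated in the article rather than merely left open. The system-perspective ROI counts gross revenue from all services as return, while the cost of delivering services outside the weight-prioritized visits is neither collected nor subtracted. The practice-perspective ROI does not share the problem to the same degree.

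The sign is wrong whenever implementation cost < extra revenue < implementation cost/m. This rests on the conventional reading of ROI and on m, which must be assumed. The window is wide at low margins and narrow at high ones, and the probability of falling inside it cannot be computed from the documents.

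This is a secondary economic analysis. It has no bearing on the primary or secondary effectiveness outcomes, but it limits what may be concluded from a figure labelled ROI.

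**What to change.** In the Return on investment section:

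1. Define the system return as the difference between conditions in revenue net of the cost of delivering the billed services. Take the contribution margin from the health system's cost accounting, or apply a stated margin ratio with a sensitivity range. Avoid subtracting visit staff time twice where it is already in the implementation cost.
2. If neither can be obtained, report the result as change in system revenue per dollar of implementation cost, and do not call it ROI.

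The second option costs only wording. The first needs a finance field or a margin ratio and a little more analysis. The downside is a figure that may look less favourable. Trial conduct, effectiveness data and clinical procedures do not change.
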